## Abstract

**Background:**

Impairments of memory are commonly reported by people with traumatic brain injuries (TBI). Such deficits are persistent, debilitating, and can severely impact quality of life. Currently, many do not routinely receive follow-up appointments for residual memory problems following discharge.

**Methods/Design:**

This is a multi-centre, randomised controlled trial investigating the clinical and cost-effectiveness of a group-based memory rehabilitation programme. Three hundred and twelve people with a traumatic brain injury will be randomised from four centres. Participants will be eligible if they had a traumatic brain injury more than 3 months prior to recruitment, have memory problems, are 18 to 69 years of age, are able to travel to one of our centres and attend group sessions, and are able to give informed consent. Participants will be randomised in clusters of 4 to 6 to the group rehabilitation intervention or to usual care. Intervention groups will receive 10 weekly sessions of a manualised memory rehabilitation programme, which has been developed in previous pilot studies. The intervention will include restitution strategies to retrain impaired memory functions and compensation strategies to enable participants to cope with their memory problems. All participants will receive a follow-up postal questionnaire and an assessment by a research assistant at 6 and 12 months post-randomisation. The primary outcome is the Everyday Memory Questionnaire at 6 months. Secondary outcomes include the Rivermead Behavioural Memory Test-3, General Health Questionnaire-30, health related quality of life, cost-effectiveness analysis determined by the EQ-5D and a service use questionnaire, individual goal attainment, European Brain Injury Questionnaire (patient and relative versions), and the Everyday Memory Questionnaire-relative version. The primary analysis will be based on intention to treat. A mixed-model regression analysis of the Everyday Memory Questionnaire at 6 months will be used to estimate the effect of the group memory rehabilitation programme.

**Discussion:**

The study will hopefully provide robust evidence regarding the clinical and cost-effectiveness of a group-based memory rehabilitation intervention for civilians and military personnel following TBI. We discuss our decision-making regarding choice of outcome measures and control group, and the unique challenges to recruiting people with memory problems to trials.

**Trial registration:**

ISRCTN65792154; Date: 18 October 2012

## Background

Impairments of memory are the most common cognitive deficits reported by people with traumatic brain injuries (TBIs), affecting 40 to 60% of patients [1, 2]. These memory problems are not only persistent, but are debilitating and difficult to treat [3]. Memory deficits may also affect the extent to which patients engage with other interventions and rehabilitation. The safety of such patients can also be compromised, making them vulnerable citizens in the home (for example, forgetting to turn the stove off), community (for example, forgetting road rules), and work (for example, forgetting important documents) settings. Memory problems consequently have a devastating effect on the psychological wellbeing of the individuals and others around them [4].

Costs of morbidity due to TBI are incurred by the healthcare system and those outside it (in terms of loss of productivity due to short-term sick leave and early retirement), and through non-medical costs (for example, transformations of house or work environments, etc.). In addition, informal care by family or friends can dominate the costs of care for affected individuals. For TBI, the direct medical costs and indirect costs were estimated at $60 billion in the United States in 2000 [5]. The full costs of dealing with memory problems caused by TBI in the UK are not known. Care costs escalate when an intervention is provided on an inpatient basis, but Salazar *et al*. [6] demonstrated that the benefits of inpatient and home cognitive rehabilitation programmes for TBI, in terms of return to duty (for military personnel) or employment, were similar.

Cognitive rehabilitation is a structured set of therapeutic activities designed to retrain an individual’s memory and other cognitive functions. A narrative review [7] found cognitive rehabilitation to be beneficial for treating cognitive deficits following brain damage. There are recommendations for the provision of cognitive rehabilitation for people with acquired brain injuries (for example, European Federation of Neurological Societies Guidelines on cognitive rehabilitation [8]; National Service Framework for Long term Conditions [9]). However, recommendations are always qualified by statements that highlight the need for more research, to support the recommendations.

Some randomised controlled trials (RCTs) have demonstrated the effectiveness of cognitive rehabilitation following brain injuries. These have mainly focussed on attention, executive functions, and visual neglect, but memory rehabilitation has not been sufficiently researched [10]. Most evidence for memory rehabilitation comes from single-case experimental design studies and controlled clinical trials. The few RCTs and quasi-RCTs in this area have offered some support for the effectiveness of intervention. Wilson *et al*. [11] examined an external memory aid, Neuropage. This enabled participants to achieve more memory-related goals than when it was not available. Doornhein and de Haan [12] reported that patients who received a memory training programme performed significantly better than those in a pseudo-treatment control group on trained memory tasks, but no differences were observed on subjective ratings of everyday memory functions. Kaschel *et al*. [13] reported that imagery mnemonics significantly improved delayed recall of verbal material and reduced observer-rated reports of memory failures. However, systematic reviews on memory rehabilitation have not found evidence to support or refute the effectiveness of such programmes [14, 15]. This lack of evidence is partly due to the paucity of well-designed trials and has led a recent meta-analysis to conclude that ‘the results for memory rehabilitation are mixed and weak’ [10] (p.33). These authors suggested that ‘researchers need to reduce reliance on single-subject and single group designs’ (p.34) and recommended more RCT evidence, a view supported by others [16]. At a symposium on disorders of memory, Wilson called for ‘better evaluation of memory rehabilitation programmes’ [17] (p.e4-5). This is a conclusion that our systematic reviews of memory rehabilitation following TBI [10], stroke [18], multiple sclerosis [19] have also reached. A small scale RCT (n = 72) was conducted to evaluate a group memory rehabilitation programme [20]. Patients with memory problems were randomly allocated to one of three group treatment programmes: compensation strategy training, restitution, or a self-help attention placebo control. The results showed that there were no statistically significant differences in outcome. However, the trend in the results and the qualitatively analysed participant feedback interviews [21] indicated the interventions seemed worthy of further evaluation. These studies provided feasibility and pilot data for the present study.

Currently, TBI patients with memory problems do not routinely receive follow-up rehabilitation after the early intensive phase, even though their abilities and needs may change once discharged from clinical services. This is mainly due to the current lack of evidence of clinical and cost-effectiveness of the intervention, and resource limitations. This study seeks to address these concerns.

## Methods/Design

### Trial objectives

The primary objective is to determine whether attending a group memory rehabilitation programme is associated with subjective reports of improved management of memory in daily life when compared to a usual care (UC) control. The secondary objectives are to assess whether the intervention is associated with improvements in ‘objectively’ assessed memory abilities, participants’ ability to achieve individually set goals, health-related quality of life, and cognitive, emotional and social wellbeing. Lastly, the cost-effectiveness of the intervention will also be investigated.

### Trial design

This is a multi-centre, parallel group, randomised controlled trial (RCT).

### Site and participant recruitment

The study will be conducted in at least four centres in the UK. New centres will be activated as old ones shut down due to their participant pools being exhausted.

Participants are identified through NHS hospitals, rehabilitation centres and charities (for example, military or head injury charities). A letter will be sent to individuals who are identified as potential participants by a member of the clinical team; this letter will include a patient information sheet, a consent form and a paid reply envelope. If the potential participant is interested in taking part, he or she is requested to complete the slip and return it in the envelope directly to the Assistant Psychologist (AP). Self-referral will also be possible via public-facing information on the study website, newsletters and posters. Participants recruited via this route will be made aware that their GP may be contacted to confirm the TBI diagnosis. Recruitment is planned to cover a 25-month period.

### Informed consent

Written informed consent will be obtained by the AP. We will explain to participants that their participation is entirely voluntary and they are free to withdraw at any time; in the event of their withdrawal, any data collected up until that point would be kept by the research team. Participants will also be asked to allow the research team to have access to their clinical notes to obtain information on their clinical diagnosis, severity of injury (Glasgow Coma Scale score), time since injury, and other medical conditions. They will be asked whether they consent to a follow-up interview to assess treatment acceptability and will be informed that if allocated to the intervention group, sessions may be video-taped to ensure treatment fidelity. The GPs of consenting participants will be sent a letter to inform them of their patients’ involvement in the trial.

### Inclusion criteria

Patients are eligible for the trial if they i) were admitted to hospital with a TBI more than 3 months prior to recruitment, ii) report having memory problems as assessed at baseline, iii) are 18 to 69 years of age, iv) are able to travel to one of the study centres and attend group sessions, and v) give informed consent.

### Exclusion criteria

Potential participants will be excluded if they i) are unable or unsuitable to engage in group treatment if allocated, ii) are involved in other psychological intervention studies, or iii) have impairment of language, as assessed at baseline.

### Initial screening assessment

At the first appointment, the AP will explain the study and make clear that the initial screening assessments are required to check that the patient meets the inclusion criteria. The AP will obtain informed consent and conduct the initial assessments. The following assessments will be conducted at screening:The Everyday Memory Questionnaire-patient version (EMQ-p [22]; a subjective measure of the frequency of memory failures in daily life. We will be using a modified version of the EMQ, which has two sections: (i) frequency of forgetting of individual items and (ii) importance of each individual item to the patient.The Rivermead Behavioural Memory Test-3rd edition (RBMT-3; [23]) an ecologically valid measure of memory ability. The RBMT-3 has been used in previous studies and is the version currently used clinically.The Sheffield Screening Test for Acquired Language Disorders (SST; [24]) used to assess language ability. We will use a cut-off score <17 to determine eligibility.Premorbid level of intellectual functioning will be estimated using the National Adult Reading Test (NART; [25]).General Health Questionnaire (GHQ-30; [26]) a measure of mood.

Potential participants will be eligible to take part if they meet the following requirements:score 24 or more on Section 1 (frequency) of the EMQ OR.score below the 25th percentile on the RBMT-3.

Those who do not meet the inclusion criteria will be notified by letter to thank them for their interest in the study and a brief report of their test results will be provided if requested. Those who meet the inclusion criteria will be phoned to arrange a second assessment session if they are willing to continue. We will also check whether they can nominate a relative or friend who knows them well who would be willing to complete two questionnaires about the participant’s memory.

### Second assessment

The purpose of this assessment, conducted 2 weeks (+/- 1 week) after the first assessment, is to achieve the following:set the short- and long-term goals that individual participants would like to achieve by the end of the study (all participants set one short term and long term goal up to a maximum of five).complete the EQ5D (a health-related quality of life measure [26]).complete the service-use questionnaire.check their availability in the event they are assigned to the intervention group.collect the EMQ-r, completed by the carer/relative.

### Participant outcome assessments

Outcome assessments will occur at 6 and 12 months after randomisation. The NHS number will be supplied to the Medical Research Information Service to allow a mortality check prior to follow-up.

The primary outcome measure will be the EMQ-patient version [22]. The study will use the frequency component as the primary outcome measure and the importance component will be used to develop a scoring mechanism to develop an assessment, which takes frequency and importance into account.

Participants will receive a questionnaire pack by post, and will be requested to return this to the Nottingham Clinical Trials Unit (NCTU) as soon as possible; however, participants do have the option of requesting help in completing these questionnaires if necessary. If questionnaires have missing items or are not returned, participants will be telephoned to obtain the missing information. The questionnaire pack will consist of: the modified EMQ (patient and relative version), GHQ-30, European Brain Injury Questionnaire [27] (patient and relative versions), EQ5D [28], and a bespoke service-use questionnaire. A research assistant, who is unaware of the group allocation, will conduct the RBMT-3 and assess goal attainment.

### Minimisation of bias

The participants and APs will not be blind to the allocated treatment. The primary outcome is participant completed and sent back directly to the data entry team. The RBMT and assessment of goal attainment (secondary outcomes) will be conducted by the RA in person. To prevent unblinding, the RA will request participants not to discuss any aspect of being involved with the study. The RA will also be required to guess the treatment allocation for each participant and this will be compared later to the actual allocation, to determine the degree of unblinding.

### Randomisation

Participants will be randomised in clusters of four to six. Once four to six participants have been identified and consented, they will be randomly allocated, as a group, to intervention or usual care (UC) (1:1 ratio). The randomisation will be based on a computer generated pseudo-random code using random permuted blocks of randomly varying size, created by the NCTU in accordance with their standard operating procedure and held on a secure server. The randomisation will be stratified by study site. Access to the sequence will be confined to the NCTU IT Manager. Investigators will access the allocation for each group by means of a remote, internet-based randomisation system developed and maintained by the NCTU. The sequence of treatment allocations will be concealed from the study statistician until all interventions have all been assigned and recruitment, data collection, and all other study-related assessments are complete.

### Duration of participant participation

Figure 1 shows the expected progress of the study. Participants are in the study for approximately 13 months from the initial screening assessment (12 months from randomisation). Participants will leave the study when they have completed the 12-month follow-up.

**Figure 1 Fig1:**
[figure not shown]
**CONSORT diagram.**

### Group-based memory intervention

Each group led by an AP will consist of 4 to 6 participants. Participants will receive 10 group memory-rehabilitation sessions (1.5 hours long, once a week for 10 weeks), following a treatment manual, which was developed and tested in the previous study (a description of the manual has been published [14, 20]). The original manual has been revised following extensive consultation and feedback from participants. Qualitative research [22] also found that the group format, composition, and duration were acceptable to participants, and delivery of the intervention was feasible. The intervention will include restitution strategies to retrain memory functions, including attention retraining and strategies to improve encoding and retrieval. Compensation strategies will be taught, including internal mnemonics (such as chunking, use of first letter cues, rhymes), use of external devices (such as diaries, mobile phones, calendars), and ways of coping with memory problems. The importance of ‘errorless learning’ [29] will also be taught.

### Control group (usual care)

Participants will receive their usual clinical care. The majority of participants will no longer be receiving any formal rehabilitation. They may be attending self-help groups or services from charities supporting people with head injuries, for example, Headway.

All other clinical services will be provided as usual for both groups. This may include referral to employment rehabilitation services, self-help groups or support from specialist charities, such as Headway. Any additional input (including psychological or medical interventions) participants receive during the study will be noted from the service use questionnaire.

### Compliance with interventions

The assistant psychologist records whether participants attend each of the treatment sessions and the reasons if sessions are not attended. To ensure the fidelity of the intervention, the content of treatment will be described and analysed. This will be achieved by video recording 20 intervention sessions. Sessions will be purposively pre-selected for recording in order to include sessions from the start, middle and end of the ten-week course and recordings will be made across the intervention period. Practices for video-recording will draw upon guidance on minimizing intrusiveness of the recording [30, 31]. Methods used in previous work will be drawn on to analyse the content of training within rehabilitation contexts [32, 33]. Two independent assessors will separately analyse the video recordings using a customized score sheet to capture a variety of key elements spanning all aspects of the intervention. Assessors will code these factors as present or absent over a series of time intervals. This method has previously been used in the pilot study and was able to determine treatment fidelity without disrupting the group sessions [34].

### Sample size and justification

The sample size calculation is based on the primary outcome measure (EMQ-p frequency total score) at six months post-randomisation. The main study aim is to detect a minimum clinically relevant difference in mean EMQ-p frequency total score of 12 between the memory intervention group and the usual care group. A 12-point difference on this measure was deemed to be a clinically significant change based on our pilot data [20] and clinical interviews. A common standard deviation of 21.9 from the pilot gives an effect size of 0.55. A type 1 error of 0.05 and power of 90% were used for the calculation. A fixed effects model at the level of the four centres is assumed, with 10% of the total variation due to between-centre variation. The participants are cluster randomised into groups of 6 at the second level and a random effects model will be used with a small intracluster correlation coefficient assumed (ICC = 0.1). This ICC is likely to be small because within each centre the therapist, intervention, and delivery location do not vary. Using the ‘Optimal Design’ software with these parameters, the calculation gives 10 groups per centre. Data from the pilot study and taking account that the control group only receives usual care suggests a possible dropout rate of 20%, so 26 groups of each intervention will be required or 312 participants in total. Based on our pilot study, we estimate we will need to screen 400 participants to recruit the required 312. Clinicians at the four centres have indicated that this is an achievable target in the timeframe proposed.

### Statistical analysis

Database lock will take place once all data entries have been checked and sufficient verification processes have been completed. Analyses will be completed with Stata version 11.2 or above. The psychometric properties of the instruments used will be evaluated when sufficient baseline data have been collected. The baseline characteristics will be described using appropriate summary statistics to examine balance between the two randomised groups.

The primary analysis will use a multi-level linear model with baseline EMQ score as a covariate, centre as a fixed effect and random effects, which take appropriate account of clustering according to allocated group [35, 36]. The between group comparison will be presented as the difference in mean EMQ-p score at 6 months between the two groups with a 95% confidence interval [35, 36]. Participants will be analysed as randomised (Intention to Treat) regardless of adherence with allocation. It is planned that the primary analysis will be based on participants with available data with no imputation for participants with missing outcomes. The distributions of raw outcome scores and residuals will be examined and the data suitably transformed or a non-parametric analysis employed if necessary.

Supportive analyses for the primary outcome will include imputation of missing data exploring different scenarios for the missing data, accounting for non-compliance with the group memory rehabilitation programme and adjusting for any characteristics assessed at baseline with an observed imbalance between the two groups.

All secondary variables will be presented using appropriate descriptive statistics and analysed with appropriate regression models using the same techniques as for the primary outcome. Differences between the two groups will be presented with 95% confidence intervals. All secondary analyses will be interpreted with caution as the sample size calculation is based on the primary outcome. The analyses for all the outcomes will be repeated with the 12 month follow-up data following similar distribution checks.

Full details of all statistical analyses will be given in a statistical analysis plan, which will be finalised prior to database lock.

### Health economic evaluation

The cost-effectiveness will be assessed from the perspective of the UK NHS and personal social services. The costs associated with the intervention will be determined by calculating the cost of staff time, materials, etc. used in providing the intervention. These will be compared with changes in the number of visits to GPs, hospital, prescribed medication, and social services contacts in the intervention and control groups during the investigation. The costs will be compared with the outcomes generated and a series of incremental cost-effectiveness ratios computed, including a cost/Quality Adjusted Life Year (QALY) analysis - based on changes in EQ-5D. A series of one-way sensitivity analyses will be undertaken to determine the extent to which baseline findings will change in light of parameter variation. Given the limited time duration of the study and follow-up, a decision analytic model will be constructed to determine the cost-effectiveness of the intervention from a lifetime perspective, a series of scenarios will be constructed to reflect the extent to which differential outcomes can be predicted to continue over longer time periods, using expert opinion and information available in the literature. A probabilistic sensitivity analysis will be carried out to determine the extent to which the intervention can be regarded as representing value for money.

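### The economic section bases QALYs on changes in EQ-5D, and the plan does not say whether baseline adjustment and allowance for allocated group reach QALYs and costs

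*Protocol article*

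**What the plan says.** The Health economic evaluation section plans a series of incremental cost-effectiveness ratios, "including a cost/Quality Adjusted Life Year (QALY) analysis - based on changes in EQ-5D". It describes resource use in terms of change too, covering GP and hospital visits, prescribed medication and "social services contacts in the intervention and control groups during the investigation". For uncertainty it lists one-way sensitivity analyses, scenarios within a lifetime decision model, and this: "A probabilistic sensitivity analysis will be carried out to determine the extent to which the intervention can be regarded as representing value for money". It names no baseline covariate and does not mention the groups of four to six in which people are randomised.

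The Statistical analysis section gives the primary outcome a multi-level linear model with baseline EMQ as a covariate, centre as a fixed effect and random effects for allocated group. It says secondary variables will be analysed by the same methods. The Abstract counts health-related quality of life and the EQ-5D-based cost-effectiveness analysis among the secondary outcomes.

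EQ-5D is collected before randomisation (Second assessment section) and again at 6 and 12 months (Participant outcome assessments section).

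**The concern.** Two sections of one article describe different treatments of baseline. For the EMQ, baseline is a covariate whose slope is estimated from the data. For the QALY, the wording points to a change, which fixes that slope at 1. The slope of a later EQ-5D measurement on baseline is normally below 1, so a fixed slope of 1 subtracts too much of any chance baseline difference and costs precision.

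The economic section is also silent on allocated group. The rule for secondary variables may fill that gap or may not. Cost-effectiveness is a stated objective of the trial, and QALY differences can be small relative to their sampling error. Both the choice of estimator and its standard error can therefore affect how the value-for-money result reads.

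**Working it through.** **Plan's own figures.** The article gives no numerical target for the economic analysis, so there is none to reproduce. The sample size, from which the group size and ICC are borrowed below, does reproduce: 10 groups per centre / 0.8 = 12.5, rounded up to 13; 13 x 4 centres = 52 groups, or 26 per arm; 52 x 6 = 312. It is not in dispute.

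**Inputs**
- EQ-5D times: baseline, 6 and 12 months (article).
- Group size 6, dropout 20%, ICC 0.1 for the EMQ (Sample size and justification section). Retained group size: 6 x 0.8 = 4.8.
- Correlation r between any two EQ-5D occasions: not given; assumed 0.4 to 0.8 and equal for all pairs, with equal variances (set to 1).
- ICC for QALYs and costs: not given; assumed 0.02 to 0.1.
- Form of the change-based QALY: not given; taken as 12-month area under the curve (weights 0.25, 0.5, 0.25) minus baseline.

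**Precision**
- Change-based variance: (0.75² + 0.5² + 0.25²)(1 - r) = 0.875(1 - r).
- Slope of the area under the curve on baseline: 0.25 + 0.75r.
- Baseline-adjusted variance: 0.375 + 0.625r - (0.25 + 0.75r)² = (1 - r)(0.3125 + 0.5625r).
- Ratio, adjusted to change-based: (0.3125 + 0.5625r) / 0.875.

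| r | ratio | reduction in variance |
|---|---|---|
| 0.4 | 0.61 | 39% |
| 0.6 | 0.74 | 26% |
| 0.8 | 0.87 | 13% |

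For a simple change at a single follow-up the ratio is (1 + r)/2. This is 0.70 at r = 0.4 and 0.90 at r = 0.8, a reduction of 10-30%. The size depends on the assumed form; the direction does not, for any r below 1.

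**Chance imbalance.** A baseline difference d enters the change-based estimate as (0.25 + 0.75r - 1)d = -0.75(1 - r)d. That is 45% of d at r = 0.4 and 15% at r = 0.8, with the sign reversed. For an illustrative d of 0.05 the shift is 0.0225 and 0.0075. Over repeated randomisations d averages zero, so this is random error and not bias.

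**Allocated group.** If groups were ignored, the true standard error relative to the naive one would be sqrt(1 + (m - 1) x ICC).

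| m | ICC | SE ratio | actual type I error at nominal 0.05 |
|---|---|---|---|
| 4.8 | 0.02 | 1.04 | 0.059 |
| 6 | 0.05 | 1.12 | 0.080 |
| 4.8 | 0.1 | 1.17 | 0.095 |
| 6 | 0.1 | 1.22 | 0.110 |

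**The case against.** The strongest reply is that the Statistical analysis section already covers this. It carries the primary methods over to secondary variables, and the Abstract lists the EQ-5D cost-effectiveness analysis as one. The article is also condensed and leaves full details to an analysis plan that is not shown. This stands in part: it is why missing cluster terms in one paragraph cannot be called a stated error. It does not settle the QALY, because the economic section has its own wording for it. Read literally, that wording differs from covariate adjustment, and the article does not say which governs.

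A second reply is that a change score is a reasonable correction. That is fair. Under the assumptions above it has lower variance than an unadjusted area under the curve once r exceeds 1/3. It is still no better than regression on baseline.

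A reader might infer several stronger things that the article does not support:
- *The QALYs are raw, unadjusted changes.* The text says what the QALY is based on; it neither specifies nor excludes regression.
- *The evaluation makes no use of the randomised groups.* The arms are compared; only the randomised clusters go unmentioned.
- *The result is biased by baseline imbalance.* Randomisation makes the change-based estimate unbiased on average.
- *Costs are correlated within group by construction.* That requires delivery cost to be assigned group by group, which is not stated.
- *The probabilistic analysis inherits standard errors that are too small.* The source of its distributions is not given.

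The ICC of 0.1 is also borrowed from the EMQ, and usual-care groups attend no sessions together. If it applied in the intervention arm alone, the average design effect at 4.8 per group would be (1.38 + 1)/2 = 1.19, a standard error ratio of 1.09.

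**Conclusion.** The point holds in a limited form. The economic section states a change-based QALY where the article uses covariate adjustment elsewhere, and it leaves open whether the rule for secondary variables applies to QALYs and costs. Covariate adjustment is more precise and uses data already planned. The gain is 13-39% in variance for r between 0.4 and 0.8, given the assumed area-under-the-curve-minus-baseline form and equal correlations.

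The part about allocated group is conditional. It matters only if the groups are in fact ignored, and its size (1.04 to 1.22 in standard error) rests on an ICC the article does not give. It supports a request to state the method. It does not support a finding that the value-for-money result will be overstated.

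**What to change.** In the Health economic evaluation section, replace the reference to changes in EQ-5D with: QALYs calculated as area under the EQ-5D curve at baseline, 6 and 12 months, with incremental QALYs estimated by regression on arm, centre and baseline EQ-5D. Make both changes together: at r = 0.6 an unadjusted area under the curve has 2.9 times the variance of the adjusted one, against 1.35 times for the change-based form.

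Add one sentence stating that QALY and cost differences allow for allocated group as in the Statistical analysis section.

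The cost is two sentences and slightly more analysis. Intervals may be wider once groups are allowed for. Baseline EQ-5D and group membership are already available, and the sample size of 312 is unaffected.
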